### 2.11. Data Collection and Management

Our data collection and management will be carried out under collaboration with our research associates, coordinators, and doctors. All the investigators will undergo standard operating procedures training, in which the follow-up, data collection and management should be strictly performed. The procedures and results of the SQD scale scores, vital sign measurements, sample collection, and laboratory examinations will be performed and obtained under the control and supervision of doctors.

Our research coordinators are college student volunteers from Jiangxi University of Traditional Chinese Medicine who have the responsibilities of contacting patients, helping patients and doctors communicate, and checking data and cross-entry. Meanwhile, several research associates in charge of standard performance, patient compliance, completeness of data collection, and problem solving will be selected from researchers at Jiangxi University of Traditional Chinese Medicine. We will ensure that each study center has a research associate.

The confidentiality of primary CRFs will be protected after data entry. The computerized database will be saved with double password protection and exclusively used for data analysis, in which patient information will be processed anonymously. Only statistical analysis staff will have access to our database, and they will be excluded from procedures other than data analysis.

### 2.12. Patient Compliance

To enhance patient compliance, the following measures will be adopted: (1) we will fully assess patients' compliance at the stage of eligibility screening to exclude patients with the consideration of poor compliance; (2) we will provide a traffic subsidy (100 China Yuan) to the participants for each follow-up. (3) A 3-day deviation in follow-up will be accepted at weeks 2, 4, and 8, and a 7-day deviation will be acceptable at weeks 26, 52, 78, and 104. (4) We will establish a WeChat (a smartphone application) group to keep in online touch with the patients and provide health counselling services to improve patients' enthusiasm. (5) For all samples allocated to patients, a recycling check will be conducted to ensure patient compliance and to confirm the correct intake dose.

### 2.13. Discontinuation and Withdrawal

After the assessment of previous compliance, study of the corresponding participant will be discontinued for the following reasons, and the participant will be withdrawn without laboratory examination.The symptoms of SQD worsen and the patient must be treated with an alternative regimen to improve his/her statusThe SAEs occurred. All SAEs will be reported by our principle investigators to the ethics committee of the local hospital and the Jiangxi Food and Drug Administration Agency within 24 hours. Several emergency measures will be taken to minimize the harm to patients when a SAE occurred. We will immediately assign senior doctors to implement rescue measures according to the corresponding guidelines. If acute toxicity caused by overdose is determined, the doctors will give measures to accelerate the drug excretion, and, if necessary, the intensive care (e.g., electrocardiograph monitoring and assisted respiration) will be performed until patients' vital signs are stable. If the patient is unable to come to the research hospital, we will advise him/her to visit the local hospital and give consultation with the local doctors, and, if necessary, we will appoint senior doctors to the local hospitalThe patient decides to take prohibited drugs to improve NOGDsPoor compliance includes an intake dose less than 80% of that required or two follow-ups beyond the specific deviation rangeParticipant has personal concerns

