#### 2.7.3. Safety Outcomes

Incidence of adverse events (AEs), including abnormal ECG and dramatic changes (indicated by a value outside 2 × the lower or upper normal reference interval) in alanine transaminase (U/L), aspartate aminotransferase (U/L), total bilirubin (*μ*mol/L), direct bilirubin (*μ*mol/L), indirect bilirubin (*μ*mol/L), or serum creatinine (*μ*mol/L). In addition, doctor-observed and patient-reported AEs are also included.SAEs are those AEs that could result in treatment in the hospital, a longer in-hospital stay, transfer to an intensive care unit, disability, life-threatening complications, and death.Treatment-related AEs defined as those AEs fully meet the following condition [17]: (1) the occurrence time is logically related to treatment administration; (2) the adverse effects cannot be interpreted by cointerventions and comorbidities; (3) the adverse effects should relieve or disappear when the treatment is withdrawn; (4) the relation is supported by definitively pharmacological or phenomenological mechanism.Withdrawal was due to AEs.

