### 2.10. Statistical Analysis

We will conduct an interim analysis at week 52 and a final analysis at week 104 with the help of the statistical software SPSS v23.0.

Specifically, an intention-to-treat analysis will be adopted for primary outcomes, while the per-protocol analysis will be performed as a sensitivity analysis. The last observation carried forward method will be used for missing data due to loss to follow-up. Continuous and categorical variables will be analyzed by t-test (or analysis of variance) and Pearson chi-squared test, respectively. In addition, continuous variables with a skewed distribution will be compared with the nonparametric rank-sum test. A P value ≤ 0.05 will indicate statistical significance for all the comparisons mentioned above, and group sequential method will be used to adjust the significant boundary for multiple t-test [19]. Subgroup analysis stratified by type of NOGDs (nonatrophic gastritis versus functional gastrointestinal disorders) and infection of* Helicobacter pylori* (yes versus no) will be performed. Furthermore, an analysis based on safety data set with no imputation will also be conducted. The incidence of AEs in the two groups will be compared using the Pearson chi-squared test, and all the AEs will be described in detail.

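### Section 2.13 makes stopping the product the end of study participation, without a laboratory examination, which weakens the intention-to-treat analysis and conflicts with the laboratory safety outcomes

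*Protocol article*

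**What the plan says.** Section 2.13 lists the reasons for discontinuation and attaches one consequence to all of them: "study of the corresponding participant will be discontinued for the following reasons, and the participant will be withdrawn without laboratory examination". The reasons are:

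- SQD symptoms that worsen and also require an alternative regimen;
- an SAE;
- a decision to take prohibited drugs for the NOGD;
- poor compliance, which includes intake below 80% or two visits outside the permitted deviation (3 days at weeks 2, 4 and 8, and 7 days from week 26 on, per Section 2.12);
- personal concerns.

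For SAEs the same section keeps a reporting duty: "All SAEs will be reported by our principle investigators to the ethics committee of the local hospital", among others, within 24 hours.

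On analysis, Section 2.10 states that "an intention-to-treat analysis will be adopted for primary outcomes, while the per-protocol analysis will be performed as a sensitivity analysis". On missing data it says "The last observation carried forward method will be used for missing data due to loss to follow-up". For safety, "an analysis based on safety data set with no imputation will also be conducted".

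Section 2.7.3 defines the first safety outcome as "Incidence of adverse events (AEs), including abnormal ECG and dramatic changes" in liver enzymes, bilirubin and creatinine. An AE counts as treatment-related only if it meets four conditions together, one being that "the adverse effects should relieve or disappear when the treatment is withdrawn".

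Section 2.9 allows at most 20% for withdrawal and loss to follow-up combined. Table 2 has no early-termination or post-withdrawal column.

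**The concern.** What ends in Section 2.13 is the participant's study, not only product intake. Four of the five reasons are tied to outcome, safety, use of other treatment or adherence. If the product works, worsening and recourse to other drugs should be less common in the HGMX arm, so the missing scores would depend on both prognosis and arm. A larger sample does not cure that.

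Two things are at stake. The first is the primary comparison over two years: much of what is called intention-to-treat would describe people who kept taking the product, plus frozen earlier scores for the rest. The second is laboratory safety: the panel is skipped at the moment when an abnormal value may be most informative, including after an SAE. Data that were not collected cannot be recovered at the analysis stage.

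**Working it through.** **Step 1: efficacy, Section 2.13 against Section 2.10.** An intention-to-treat analysis uses all randomised participants in their assigned arms, whatever they took. Section 2.13 removes low-intake participants and users of prohibited drugs from the study, and no assessment is scheduled for them afterwards. Three things follow.

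- Their week-52 and week-104 scores must be imputed. The only method named is LOCF, and it is stated for loss to follow-up. Whether it also covers withdrawal that the protocol itself requires is not said.
- LOCF keeps the last score before withdrawal. A participant withdrawn for worsening between weeks 26 and 52 would carry the week-26 score, which may predate the worsening. One withdrawn before week 2 has a change of 0.
- The per-protocol set consists mainly of adherers, and the observed late scores in the intention-to-treat set come from much the same people. The sensitivity analysis can therefore reveal little about the effect of excluding non-adherers.

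Gastroscopy is done only at baseline and the last visit (Section 2.8), so an early withdrawer has no follow-up value for that secondary outcome.

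**Step 2: safety, Section 2.13 against Sections 2.7.3 and 2.10.** Laboratory changes are safety outcomes and the safety analysis imputes nothing. A value not taken at withdrawal is therefore simply absent. The condition that an effect recede once treatment stops needs an observation after stopping. For a laboratory abnormality in a withdrawn participant, the plan schedules none.

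**Step 3: how much of the loss allowance one rule could use.** The documents give no rate of late visits, so the risk q per visit is an assumption, taken as independent across visits. There are seven post-baseline visits (weeks 2, 4, 8, 26, 52, 78 and 104). A second breach at week 104 leaves nothing later to lose, so only the first six count:

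P(at least 2 of 6) = 1 − (1 − q)^6 − 6q(1 − q)^5

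| q (assumed) | Calculation | P | Of 200 |
|---|---|---|---|
| 5% | 1 − 0.7351 − 0.2321 | 3.3% | about 7 |
| 10% | 1 − 0.5314 − 0.3543 | 11.4% | about 23 |
| 15% | 1 − 0.3771 − 0.3993 | 22.4% | about 45 |

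The allowance for all causes is 20% of 200 = 40.

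**Step 4: precision is not the problem.** From Section 2.9 (difference 6.0, SD 13.0, α 0.05 taken as two-sided, power 80%):

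n per arm = 2 × (1.960 + 0.842)² × 13² / 6² = 73.7, so 74; 74 / 0.8 = 92.5, so 93; total 186.

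The planned 200 is slightly above this. With 20% lost, 80 per arm remain, and power = Φ(6 / (13√(2/80)) − 1.96) = Φ(0.959) = 0.83. The allowance covers the loss of numbers. It does not cover bias.

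**The case against.** Several stronger readings are tempting, and the text does not support them.

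- *Everyone who worsens is removed.* No: worsening counts only when an alternative regimen is also needed.
- *No further data are collected.* This is a reasonable inference from discontinuing the participant's study and from the absence of later visits in Table 2, but it is not written. Only the omission of the laboratory examination is explicit.
- *Intention-to-treat is impossible.* No: all randomised participants can be analysed in their assigned arms with carried-forward values. The analysis is compromised, not ruled out.
- *The key safety data are lost.* Only in part. SAEs are still reported and managed, withdrawal due to AEs is itself a safety outcome, and laboratory and ECG results from earlier visits remain. What is missing is a panel at withdrawal and later follow-up. A bias of the safety comparison towards no difference is plausible but not shown.
- *The window rule alone uses up the allowance.* Only at the upper end of an assumed range. Counting all seven visits would give 4.4%, 15.0% and 28.3%, but that includes second breaches at week 104, which cost no later data.

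It can also be said that an article condenses the full protocol, and that the Discussion (Section 3) already admits attrition bias. The first would answer a mere silence, but Section 2.13 states affirmatively that the study is discontinued and the laboratory examination omitted. The second concerns loss to follow-up as something probably unavoidable; the attrition here is created by the protocol's own rule.

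**Conclusion.** The point holds in this form: Section 2.13 ties leaving the study to stopping the product, for reasons that are mostly related to outcome, safety or adherence. Followed as written, it produces missing SQD scores that are likely to be informative, weakens the promise that "an intention-to-treat analysis will be adopted for primary outcomes", and leaves the per-protocol analysis with little to add. The omitted laboratory examination cannot be squared with Sections 2.7.3 and 2.10 as they stand.

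The size of the bias cannot be derived from the documents, because neither the withdrawal rate nor its split by arm is given. The 3.3% to 22.4% range covers one administrative reason only and rests on the assumed, independent breach risks. It does not measure the outcome-related missingness, which is the main worry. That assessments stop after withdrawal is an inference, though the natural one. The matter belongs in the protocol, because an analysis plan cannot restore data that were never collected.

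**What to change.** Leave every reason for stopping the product unchanged, and amend the wording so that:

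1. stopping the product and leaving the study are separate events;
2. a participant who stops continues the scheduled SQD-scale, AE and laboratory/ECG assessments unless consent is withdrawn;
3. all SQD scores collected, including late ones, enter the intention-to-treat analysis, while adherence and window deviations are handled in defining the per-protocol set;
4. the omission of the laboratory examination in Section 2.13 is reconciled with the laboratory outcomes and the causality condition in Section 2.7.3 and with the safety analysis in Section 2.10;
5. Section 2.10 says how scores still missing after withdrawal are treated, since LOCF is now stated only for loss to follow-up.

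The cost is wording plus some effort to retain people who have stopped, within visits already scheduled for them. The estimated effect may also be smaller, because scores after stopping are included. With all 100 per arm followed and an assumed 20% stopping, the difference becomes 6.0 × (1 − 0.2 × 0.5) = 5.4 if stoppers keep half the effect, and 6.0 × (1 − 0.2) = 4.8 if they keep none. Power, as Φ(difference / (13√(2/100)) − 1.96), is then 0.84 or 0.74, against 0.83 for 80 completers per arm at the full 6.0. At 10% stopping the corresponding powers are 0.87 and 0.84; at 30%, 0.79 and 0.63. That possible loss of power is the price of an estimate that reflects everyone randomised.

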## 3. Discussion

Since the 20th century, the disease spectrum has undergone significant changes: the chronic diseases, such as nonorganic disorders, diabetes mellitus, cardiovascular diseases, and cancer, become the major disease burden. The development of these diseases is multifactorial and the diet often plays an important role. Thus, diet-related management (e.g., diet control and nutrition supplement) could be a treatment approach for these diseases. However, the clinical nutriology simply based on adjustment of diet structure has limitations on the efficacy.

Using the TCM theory, the food (including herbs in the list of food) can be made into dietary TCM formula, which can be daily eaten and has treatment effects for chronic diseases. HGMX is a dietary TCM formula developed based on this concept. After screening of a large number of classic TCM formula, Shen Ling Bai Zhu San was chosen as the basic formula of HGMX, because its efficacy and safety for gastrointestinal diseases are validated by thousands of years of application and animal and clinical researches. On the other hand, except for atractylodes, all components of Shen Ling Bai Zhu San are in the official list of food designated by the Ministry of Health of China. Thus, it can be easily modified to a pure dietary formula on the premise without changing the main effects. During the two years of marketing, no adverse events related to HGMX are reported. Therefore, the safety of this RCT can also be guaranteed.

To validate the potential effects of HGMX on gastrointestinal protection and systemic symptom improvement, we intend to perform a series of RCTs. The study series contains 3 RCTs, with the other two focusing on patients with peptic ulcers (NCT03320538) and on patients who underwent radical gastrectomy for gastric cancer (NCT03025152). These RCTs are also corresponding to three main applications of dietary TCM formula: (1) use for the treatment of nonorganic disorders; (2) adjuvant therapy for the treatment of chronic diseases; and (3) adjuvant therapy for the rehabilitation of major diseases.

The main purpose of this RCT is to clarify the long-term efficacy, safety, and compliance of HGMX, as a dietary TCM formula, in patients with SQD and NOGDs, with the guidance of TCM theory and evidence-based medicine methodology. The randomization of this RCT is standardly designed to minimize the selection bias and the period of follow-up is enough to observe the long-term efficacy and safety. Before the beginning of the trial, we appointed a training group contained senior methodologists, pharmacists, and physicians to conduct a standard operation procedure training in each research hospital. The diagnosis of TCM syndrome and the measurement of patient-reported outcomes will be performed by well-trained TCM physicians according to the standards to increase the consistency between difference investigators and hospitals. We also prespecified two sets of subgroup analysis based on expert's opinion and biological mechanism and used the group sequential method in repeated measures to reduce the probability of type I error. The results of the trial will be reported in strict accordance with the checklist of Consolidated Standards of Reporting Trials (CONSORT) Extension for Chinese Herbal Medicine Formulas. Therefore, this RCT can be expected to produce high-quality evidence.

This study may have some limitations. First, we will use an adjusted scale to assess SQD symptoms without reliability and validity tests, which could introduce a detection bias. We will conduct reliability and validity tests based on our study outcome data to test whether there exist any defects in reliability and validity. Second, because the placebo consists of early rice and oats and will be undertaken regularly according the study protocol, the patients in the placebo group may correct some bad diet habits during the participation, which may have positive effects on NOGDs and lead to bias in results (i.e., the estimate may tend to be conservative). Third, although we will take various measures to improve the patient compliance, the loss to follow-up is still probably inevitable during the long-term follow-up, resulting in attrition bias.

The dietary TCM formula is currently becoming a hot concern in the area of TCM owing to the safety attribute of diet and the therapy attribute of herb. However, the incomplete industry standards and evaluation methodology are restraining the development and application of the dietary TCM formula. A critical reason of these problems is the extreme scarcity of high-quality evidence. Therefore, using rigorous methodology to evaluate efficacy and safety of the dietary TCM formula in the framework of evidence-based medicine is a necessary approach to address these issues. We hope to take the first step to produce high-quality evidence for the dietary TCM formula by carrying out this RCT series, which will establish a reference for the future clinical researches of other dietary TCM formulas and will be of important value in developing related regulations.

## Figures and Tables

**Figure 1 fig1:**
[figure not shown]
Overall design of the study.

**Table 1 tab1:** Detailed components of Hou Gu Mi Xi.

Component	Part used	Proportion
Renshen (ginseng)	Root	1.67%
Fuling (tuckahoe)	Sclerotium	6.67%
Yiyiren (coixenolide)	Seed	6.67%
Shanyao (Chinese yam)	Root	3.33%
Lianzi (lotus seed)	Fruit	3.33%
Sharen (amomum)	Fruit	0.33%
Jiegen (Platycodon)	Stem	1.67%
Baibiandou (white hyacinth bean)	Seed	6.67%
Gancao (licorice)	Stem	1.67%
Jupi (orange peel)	Pericarp	1.67%
Early rice	Seed	43.22%
Oats	Seed	23.10%

**Table 2 tab2:** Procedures of the trial.

Item	Baseline	2^nd^ week	4^th^ week	8^th^ week	26^th^ week	52^th^ week	78^th^ week	104^th^ week
Eligibility screening	√							
Signed inform consent	√							
Spleen Qi Deficiency Symptoms Grading and Quantifying Scale	√	√	√	√	√	√	√	√
Physical examination (height, weight, blood pressure, heart rate)	√	√	√	√	√	√	√	√
Blood, urine, and stool routine examination	√			√	√	√	√	√
Electrocardiogram	√			√	√	√	√	√
Liver function (ALT, AST, TBIL, DBIL, IBIL)	√			√	√	√	√	√
Kidney function (Scr, BUN)	√			√	√	√	√	√
Gastric function (Gastrin-17)	√					√		√
Helicobacter Pylori	√							
Gastroscopy	√							√
Record of adverse events				√	√	√	√	√
Compliance assessment		√	√	√	√	√	√	√

ALT = alanine transaminase, AST = aspartate aminotransferase, TBIL = total bilirubin, DBIL = direct bilirubin, IBIL = indirect bilirubin, SCr = serum creatinine, BUN = urea nitrogen, and PT= prothrombin time.

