### 2.6. Interventions

Our participants are grouped into the HGMX group (experimental group) and the control group. In the HGMX group, participants will be treated with an oral dose of 30 g/day HGMX. Every 30 g of HGMX contains 10.1 g of herbal material (detailed components of HGMX are shown in Table 1) and 19.9g early rice and oats. Participants in the control group will receive the same dose of placebo, which consists of 66.7% early rice and 33.3% oats with the same preparation, packaging, labeling, and appearance but a slightly different taste and smell than the real HGMX. All subjects will be treated for a duration of 2 years (104 weeks). During follow-up, patients can be treated as necessary based on clinical guidelines for acute and chronic diseases (such as hypertension, diabetes, and osteoarthritis) that are not included in the exclusion criteria.

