### 2.8. Study Follow-Up and Outcome Assessments

The durations of follow-up and treatment are equal at 2 years. In our study, all participants will be evaluated 8 times: at baseline and in weeks 2, 4, 8, 26, 52, 78, and 104. After the qualified participants sign the informed consent form, they will document the characteristics of their own symptoms in the baseline case report form (CRF) and then record the baseline (first visit) physical and laboratory examination data. In weeks 2 and 4, participants will complete the Spleen Qi Deficiency Symptoms Grading and Quantifying Scale (SQD scale) and a physical examination. In weeks 8, 26, 52, 78, and 104, an ECG and laboratory examination, including routine blood, urine, and stool tests, are required. Gastrin-17 and* Helicobacter pylori* will be assessed at both weeks 52 and 104. Gastroscopy will be performed at only baseline and the last visit.  Table 2 provides an overview of the study procedures.

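### Adverse events are first scheduled for recording at week 8, so non-serious early events rest on recall although participants are seen at weeks 2 and 4

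*Protocol article*

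**What the plan says.** Section 2.8 sets the visits: "all participants will be evaluated 8 times: at baseline and in weeks 2, 4, 8, 26, 52, 78, and 104". Table 2 assigns procedures to them. Its row "Record of adverse events" is blank at baseline, week 2 and week 4, and ticked at weeks 8, 26, 52, 78 and 104. The two early visits do take place: Table 2 ticks the SQD scale, the physical examination and the compliance assessment at both.

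Section 2.8 describes the early visits as follows: "In weeks 2 and 4, participants will complete the Spleen Qi Deficiency Symptoms Grading and Quantifying Scale (SQD scale) and a physical examination".

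Section 2.7.3 defines the safety outcomes. After listing ECG and laboratory abnormalities it adds that "doctor-observed and patient-reported AEs are also included". It also makes withdrawal because of an AE an outcome. Neither has a start date or time window.

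Section 2.13 deals with serious events separately: "All SAEs will be reported by our principle investigators to the ethics committee of the local hospital", within 24 hours and without reference to a visit. For discontinuation it says that "the participant will be withdrawn without laboratory examination". It names no AE check at that point.

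**The concern.** Safety is a stated objective alongside efficacy, and section 2.6 has participants taking the product daily for 104 weeks. Intolerance of a newly started food product could plausibly appear soon after first intake, yet the two visits closest to first intake carry no AE record.

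Three outcomes are exposed:

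- **Incidence of non-serious AEs.** A mild reaction that has resolved by week 8 is recorded only if the participant recalls it.
- **Treatment-related AEs.** Section 2.7.3 requires, among other conditions, a plausible time relation to treatment and relief once treatment is withdrawn. Both are harder to judge when onset and resolution are noted weeks later.
- **Withdrawal due to AEs.** A participant who leaves before week 8 has no scheduled AE record. The reasons for discontinuation in section 2.13 include serious events, worsening SQD symptoms, poor compliance and personal concerns, but not a non-serious AE. A withdrawal over mild intolerance could be filed under one of the last two.

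Section 2.10 analyses safety data without filling in missing values and compares AE incidence by a chi-squared test, so an unrecorded event counts as no event.

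**Working it through.** The plan states no expected AE rate and no figure that depends on this schedule, so there is nothing to reproduce. The check is a reading of the schedule, followed by simple arithmetic.

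**1. Is the blank real?** The AE row has eight visit cells: three blank, then five ticks. The row beneath it, compliance assessment, is ticked at weeks 2 and 4, so this does not look like a misaligned table. The AE ticks fall exactly on the post-baseline ECG and laboratory visits. That may explain the pattern, but events seen by a doctor or reported by a patient need no test.

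**2. How far does section 2.8 support it?** It is consistent with Table 2 but is weaker evidence. It names AE recording at no visit, and it omits the compliance assessment that Table 2 ticks at weeks 2 and 4. Table 2 carries the point.

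**3. Visits and exposure affected** (visits from section 2.8, duration from section 2.6)

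- Post-baseline visits without AE recording: 2 of 7 (weeks 2 and 4).
- Exposure before the first AE record: 8/104 = 7.7%.
- Exposure before the week-4 visit: 4/104 = 3.8%. This is the part whose recording at a visit the two ticks would change; events in weeks 4-8 would still first be recorded at week 8.

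**4. Possible loss.** Let p be the share of non-serious AEs that start in weeks 0-8, and r the share of those recovered by recall at week 8. Then

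share missed = p × (1 − r).

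The article gives neither p nor r, so both are assumed:

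| p (assumed) | r = 0 | r = 0.5 | r = 0.8 | r = 1 |
|---|---|---|---|---|
| 7.7% (constant rate) | 7.7% | 3.8% | 1.5% | 0% |
| 25% | 25% | 12.5% | 5% | 0% |
| 50% | 50% | 25% | 10% | 0% |

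Every row includes zero. The table shows what the loss depends on; it does not estimate it.

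**5. Effect of adding the two ticks.** AE-recording visits rise from 5 to 7 of 7. The first look-back shortens from 8 weeks to 2. A participant who leaves between weeks 2 and 8 has at least one scheduled AE record. Sample size, power and alpha do not change.

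**The case against.** The strongest reply is that no loss is shown. Nothing says that the week-8 record excludes events since first intake, just as the week-26 record must cover weeks 8-26. This stands. A reader might infer from Table 2 that the safety outcome is undercounted; the article supports only that it may be.

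A second reply is that recall is not peculiar to the early period. The intervals up to the successive AE records are 8, 18, 26, 26 and 26 weeks, so the one criticised is the shortest. That is correct, and recall alone does not single out early events. The difference is that no visit falls inside the later intervals, whereas here two visits take place without AE recording.

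A third is that other routes exist. Serious events are reported within 24 hours, section 2.7.3 sets no window, and section 2.12 describes online contact with patients. These reduce the risk, but the 24-hour rule covers serious events only, and the article does not say that the online contact is used to record AEs. The full protocol or the case report form may contain look-back wording. That lowers the severity, but it does not alter a schedule that Table 2 states outright.

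Finally, a reader might infer bias in favour of HGMX, since only that arm receives the herbal ingredients. The article does not establish this. Both arms start a new daily 30 g product under blinding and follow the same schedule, and a known allergy to the components is an exclusion (section 2.4). A shared gap mainly lowers absolute incidence in both arms.

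**Conclusion.** The point holds as a weakness in the AE schedule. Table 2 omits AE recording at two visits that take place on treatment, section 2.8 does not supply it, and this fits poorly with safety outcomes that section 2.7.3 defines without a start date. Non-serious events in the first weeks depend on recall at week 8. They may be missed if mild and resolved, or if the participant leaves first.

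The size of any loss is unknown and may be zero. Only the exposure shares and the visit count are exact; any figure for the share of early-onset events or for recall is an assumption. Distortion between arms requires early AEs or early drop-out to differ by arm, which the article neither shows nor rules out. The matter should be fixed. It does not threaten the primary analysis.

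**What to change.** In Table 2, tick "Record of adverse events" at weeks 2 and 4. In section 2.8, state that AEs are recorded at every contact from first intake until the last visit or withdrawal. That sentence also settles when recording starts, which sections 2.7.3, 2.8, 2.13 and Table 2 leave open between them. It covers participants who leave before week 2, whom the ticks alone would not reach.

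The cost is one more case report form page at two existing visits. The reported AE count may rise slightly.
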